### Secondary endpoints

1. Primary safety endpoint will be the occurrence of any grade 3 adverse event (AE) or serious adverse event (SAE), from the commencement of each study arm until 6 months thereafter; such events may be related or unrelated to study procedure.
2. Safety & tolerability will additionally be assessed by the occurrence of all (grade 1-2) adverse events at least possibly related to study therapy, from the commencement of each study arm until 6 months thereafter.
3. Proportion of subjects without peripheral microfilaraemia at 6 months follow up
4. Median reduction of *L. loa* MF at each month post start of treatment and at nadir
5. Median time from commencement of treatment to nadir of *L. loa* microfilaraemia

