# Procedures

## Study schedules

Arms 1+2 will commence simultaneously; after arms 1+2 have started, arms 3+4 will also start in parallel. Basic follow-up schedules will be similar for subjects in all 4 arms: visits will take place at screening, immediately prior to commencement of the study arm and thereafter daily for the first week, twice per week for the subsequent two weeks (i.e. until the end of the first albendazole course in arms 2-4) and thereafter once per week until the second course of treatment commences in arms 3+4. This second round of treatment will commence as soon as 90% of the subjects still in follow-up in arm 4 drop below the threshold of 4000 mf/mL. A similar visit schedule will then be used for the second treatment round in arms 3+4 (daily during the first week of treatment and twice per week during the second week). Thereafter, twice monthly follow up visits will be scheduled for the remaining follow-up period until the end of follow-up at 6 months.

### Arm 1

No anti-helminthic medication will be used, although symptomatic treatment may be provided if deemed clinically appropriate. Participants will be seen at screening, immediately prior to commencement of the study arm and thereafter daily for the first week, twice per week for the subsequent two weeks and thereafter once per week until eight weeks after start of the study arm and then twice monthly until the end of follow-up at 6 months. At the end of the study, any participants in this arm who wish to, will be provided with a 3-week course of albendazole (400mg/day), in line with Gabonese national guidelines for MDA in Loa-endemic populations. Note that no further follow-up will be performed during this treatment course.

### Arm 2

A single 3-week course of albendazole (800mg/day) will be provided at commencement of the study arm, simultaneously with the start of Arm 1. Participants will be seen at screening, immediately prior to commencement of the study arm and thereafter daily for the first week, twice per week for the subsequent two weeks (until the end of the albendazole course) and thereafter once per week until eight weeks after start of the study arm and then twice monthly until the end of follow-up at 6 months.

### Arm 3

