A single 3-week course of albendazole (800mg/day) will be provided at commencement of the study arm, simultaneously with the start of Arm 4. Participants will be seen at screening, immediately prior to commencement of the study arm and thereafter daily for the first week, twice per week for the subsequent two weeks (i.e. until the end of first albendazole course) and thereafter once per week until 90% of the subjects still in follow-up in arm 4 drop below the threshold of 4000 mf/mL; if this criterion is not yet achieved by week 8, subsequent visits will be reduced to twice monthly. All participants will then be re-treated with a 2-week course of albendazole (800mg/day). All subjects will be seen daily for follow-up visits during the first week of re-treatment and twice per week during the second week. Thereafter further follow-up visits will take place twice monthly until the end of follow-up at 6 months.

### Arm 4

A single 3-week course of albendazole (800mg/day) will be provided at commencement of the study arm, simultaneously with the start of Arm 3. Participants will be seen at screening, immediately prior to commencement of the study arm and thereafter daily for the first week, twice per week for the subsequent two weeks (i.e. until the end of first albendazole course) and thereafter once per week until 90% of the subjects still in follow-up in arm 4 drop below the threshold of 4000 mf/mL; if this criterion is not yet achieved by week 8, subsequent visits will be reduced to twice monthly. All participants with <4000 mf/mL will then be treated with a single dose of ivermectin; any subjects *not* achieving <4000 mf/mL at this time point will instead commence continuous re-treatment with *albendazole* until microfilaraemia becomes undetectable, until treatment is no longer tolerated, or until the end of follow-up (whichever occurs first). *All* subjects will be seen daily for follow-up visits during the first week following ivermectin/albendazole (re-)treatment and twice per week during the second week. Thereafter further follow-up visits will take place twice monthly until the end of follow-up at 6 months.

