### Visits during intake of albendazole

Once daily visits will be performed during the first week of all study arms, including observed intake of one daily dose of albendazole in arms 2-4 and recording of AEs in all. For the two weeks thereafter, visits will be performed twice weekly. Patients will be specifically and repeatedly advised that albendazole intake shall follow intake of a standard meal as this importantly enhances the bioavailability of albendazole. Note that intake of albendazole on non-visit days and the intake of the *second* dose on visit days will not be supervised. Blood samples will be drawn for laboratory safety parameters (haematology and biochemistry) and quantification of microfilaraemia on the 1^st^ day after start of treatment (DT+1), DT+3, DT+7, DT+10, DT+14, DT+17 and DT+21. In arm 1, blood samples will be drawn for the quantification of microfilaraemia according to a similar schedule. At DT+14 additional blood may be collected for immunology in all study arms. (*Visit designations are approximate and may vary by ±1 day in the first week after start of treatment and by ±2 days in the two weeks thereafter.*).

If clinically indicated a physical examination and/or additional blood draw(s) for laboratory safety parameters will be performed.

Subjects in arm 3 (and subjects in arm 4 who failed to achieve <4000 mf/mL) will undergo a similar schedule of visits during their second course of albendazole, commencing on the first day of re-treatment (DRT0) except that these visits will last only until DRT+14, instead of DRT+21. Additional blood may be collected for immunology at DRT0 and DRT+14. (*Visit designations are approximate and may vary by ±1 day in the first week after start of treatment and by ±2 days in the week thereafter.*)

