### Visits following intake of ivermectin

Subjects in arm 4 who achieve <4,000 mf/mL will receive a single dose of ivermectin under observation, followed by daily visits to record AEs during the first week after intake and twice weekly in the second week. Blood will be drawn for laboratory safety parameters (haematology and biochemistry) and quantification of microfilaraemia on the day of treatment (DRT0), DRT+1, DRT+3, DRT+7, DRT10 and DRT+14. Additional blood may be collected for immunology at DRT0, DRT+1 and DRT+14. (*Visit designations are approximate and may vary by ±1 day in the first week after start of treatment and by ±2 days in the week thereafter.*)

If clinically indicated a physical examination and/or additional blood draw(s) for laboratory safety parameters will be performed.

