### Follow-up visits

In arms 1+2, weekly follow-up visits will take place from week 4 through week 8; thereafter, twice monthly visits will take place until the end of follow-up (at month 6). In arms 3+4 weekly follow-up visits will take place between the first and second courses of treatment; if re-treatment has not started by week 8, then these visits will be reduced to twice monthly. Twice monthly visits will also take place from two weeks after commencement re-treatment until the end of follow-up (at month 6) in arms 3+4. AEs will be recorded and blood drawn for quantification of microfilaraemia at each visit. Additional blood may be collected for immunology and laboratory safety parameters at the end of follow-up (at month 6) in all study arms. If clinically indicated a physical examination and/or additional blood draw(s) for laboratory safety parameters will be performed. At day 28, day 63 and at 6 months an additional pregnancy test will be performed in female subjects.

The investigator will collect pregnancy information on female participant who becomes pregnant during drug intake or three months after the last dose of study drug. The participant will be follow up to delivery and the neonate information will also be collected. Any termination of pregnancy will be reported.

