## SAEs

An AE is considered “serious” if it results in any of the following outcomes:

• Death

• A life-threatening situation

• Inpatient hospitalization or prolongation of existing hospitalization

• Persistent or significant disability/incapacity defined as a “substantial disruption of the ability to conduct normal life functions”

• Congenital anomaly/birth defect (in the offspring of a subject)

An AE or suspected adverse reaction is considered “life-threatening” if its occurrence places the patient or subject at immediate risk of death. It does not include an adverse event or suspected adverse reaction that, had it occurred in a more severe form, might have caused death.

Important medical events that may not result in death, be life-threatening, or require hospitalization may be considered serious when, based upon appropriate medical judgment, they may jeopardize the patient or subject and may require medical or surgical intervention to prevent one of the outcomes listed in this definition. Examples of such medical events include allergic bronchospasm requiring intensive treatment in an emergency room or at home, blood dyscrasias or convulsions that do not result in inpatient hospitalization, or the development of drug dependency or drug abuse.

SAEs must be reported to the safety monitor and responsible ethical committee within 24 hours.

SAEs will be collected and recorded from all participants throughout the trial, from the moment of inclusion until the end of follow-up (i.e. 6 month after commencement of each study arm).

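### AE and SAE collection is not tied to the last dose, and on continuous albendazole in arm 4 no safety panel is clearly fixed between DRT+14 and month 6

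*Protocol*

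**What the plan says.** **Collection window.** Section 4.3.2, item 1, collects grade 3 AEs and SAEs "from the commencement of each study arm until 6 months thereafter; such events may be related or unrelated to study procedure". Item 2 uses the same window for related grade 1-2 events. Section 7.6 collects SAEs "until the end of follow-up (i.e. 6 month after commencement of each study arm".

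**Start of re-treatment (DRT0).** The second round in arms 3 and 4 starts "as soon as 90% of the subjects still in follow-up in arm 4 drop below the threshold of 4000 mf/mL" (6.1). No latest date is given. If the trigger is slow, only the visit frequency changes: "if this criterion is not yet achieved by week 8, subsequent visits will be reduced to twice monthly" (6.1.3, 6.1.4).

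**Continuous albendazole.** Arm 4 participants who are not below the threshold at that time take 400 mg twice daily "until microfilaraemia becomes undetectable, until treatment is no longer tolerated, or until the end of follow-up (whichever occurs first" (6.1.4).

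**Safety bloods.** The re-treatment schedule follows the first course "except that these visits will last only until DRT+14, instead of DRT+21" (6.2.2). Ivermectin recipients have their own schedule to DRT+14: "Blood will be drawn for laboratory safety parameters (haematology and biochemistry) and quantification of microfilaraemia on the day of treatment (DRT0", and onwards (6.2.3). After that, 6.2.4 provides: "AEs will be recorded and blood drawn for quantification of microfilaraemia at each visit". Safety bloods at these later visits depend on a clinical reason. A month-6 safety draw is offered in all arms, worded as optional in 6.2.4, while the V3 entry in the document history says that this analysis will be done without a clinical reason.

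**The concern.** Safety and tolerability of the regimens is a secondary objective (4.2.2), and an abnormal laboratory finding counts as an AE (7.2). A window counted only from arm start leaves whatever time happens to remain after the last dose. For a participant still on albendazole at month 6, nothing remains.

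The laboratory side has a similar gap. The first 21-day course has panels at seven time points after the start of treatment (6.2.2). A longer exposure at the same daily dose has fixed panels only up to DRT+14. One stopping rule for continuous albendazole is intolerance, yet no interim panel is clearly fixed to show liver or blood changes that cause no symptoms.

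This is a matter of what gets collected, so an analysis plan could not restore it. Section 6.2.4 does count from the last dose for pregnancy (three months), but nothing similar exists for AEs or SAEs.

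**Working it through.** **Inputs.** Month 6 is taken as day 182 (an assumption; days 180 to 183 shift every result below that depends on it by -2 to +1 days). The arm 3 second course lasts 14 days in 6.1.3 and 21 days in 6.3.1, so both are shown. The protocol's own size is reproduced: 8/(1 - 1/3) = 12 per treatment arm, and 3 x 12 + 6 = 42 in total. Here it matters only because it puts 8 to 12 participants in arm 4 follow-up.

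**1. Days observed after the last dose.** Ivermectin: 182 - DRT0. Arm 3: 182 - DRT0 - 14, or 182 - DRT0 - 21. Continuous albendazole taken to month 6: 182 - 182 = 0.

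| DRT0 (day) | Ivermectin | Arm 3, 2 weeks | Arm 3, 3 weeks | Continuous albendazole to month 6 |
|---|---|---|---|---|
| 28 | 154 | 140 | 133 | 0 |
| 56 | 126 | 112 | 105 | 0 |
| 140 | 42 | 28 | 21 | 0 |
| 154 | 28 | 14 | 7 | 0 |
| 168 | 14 | 0 | -7 | 0 |

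With re-treatment by week 8, ivermectin recipients and arm 3 have at least 105 days. If 28 days after the last dose is the yardstick, it is met when DRT0 is no later than day 154 (ivermectin), 140 (arm 3, two weeks) or 133 (arm 3, three weeks).

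**2. Interval on continuous albendazole without a clearly fixed panel.** 182 - DRT0 - 14. DRT0 at day 28: 140 days. DRT0 at day 56: 112 days. Twice-monthly visits inside the interval, leaving out month 6: 140/14 - 1 = 9 and 112/14 - 1 = 7.

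**3. How many participants can be on continuous albendazole.** When the trigger is met, the largest number not below 4,000 mf/mL is:

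| In arm 4 follow-up | Share below if one is not | At least 90% (6.1) | More than 90% (4.1) |
|---|---|---|---|
| 12 | 11/12 = 91.7% | 1 | 1 |
| 11 | 10/11 = 90.9% | 1 | 1 |
| 10 | 9/10 = 90.0% | 1 | 0 |
| 9 | 8/9 = 88.9% | 0 | 0 |
| 8 | 7/8 = 87.5% | 0 | 0 |

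**4. Are interim panels implied elsewhere?** Section 6.4.1 takes the microfilarial blood from what is left in the haematology and biochemistry tubes, which suggests that those tubes are drawn at every visit. Section 6.4.2 puts no condition on the full blood count and makes biochemistry depend on being scheduled, with treatment as its example, or on a clinical reason. Section 6.2.4, which governs these visits, names only AEs and microfilariae as routine. Read together, they do not settle whether a panel is run.

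**The case against.** The fixed window is a defensible choice. Arm 1 is untreated and has no last dose, so six months from arm start gives all four arms equal observation time, which suits a descriptive pilot. That stands, and it is why the six-month window should remain the common one.

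The reach is small. At most one of 42 participants is on continuous albendazole, and that person must also stay positive to month 6, because treatment stops once microfilariae are undetectable. An independent safety monitor is on site (7.7). This stands too.

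A reader might infer that safety bloods cease altogether at DRT+14. The protocol does not support that: a month-6 draw exists in all arms, bloods can be taken on clinical grounds at any visit, and 6.4.1 and 6.4.2 can be read as implying interim panels. A reader might also infer that events on continuous albendazole go unrecorded. They do not, since AEs are recorded twice monthly throughout, and laboratory changes still present at month 6 could be found then.

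Short post-dose time in arm 3 and after ivermectin comes mainly from the lack of a latest re-treatment date. Section 3.2.3 cites a fall to 20% of pre-treatment levels at six months on 400 mg/day. At that rate anyone starting above 20,000 mf/mL stays above 4,000 (0.20 x 20,000 = 4,000), and two such participants of 12 would hold back the trigger (10/12 = 83.3%). But the dose here is double and there is no lower entry limit, so this shows only that a late trigger is possible.

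**Conclusion.** The point holds in a narrow form and is minor. It concerns safety conduct, not the choice of analysis, and no sample size or efficacy result changes.

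Followed as written, one arm 4 participant could take 800 mg/day to month 6 with no observation after the last dose. That participant could also have no clearly fixed panel for up to 140 days (DRT0 at week 4) or 112 days (week 8). The count is at most one with 11 or 12 in arm 4 follow-up, at most one with 10 under the 6.1 wording only, and none with 9 or fewer.

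This rests on month 6 being about day 182 and on 6.1.4, which assigns continuous albendazole when the trigger is met. Sections 4.1 and 6.3.1, read alone, tie it to failure after the first course and do not repeat that limit.

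It would go too far to say that all re-treated participants lack post-dose observation. They are affected only if re-treatment starts late, and the protocol gives no expected date, so no probability is claimed. Nor does the protocol require 28 days: that figure is a convention brought in from outside it.

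**What to change.** - **6.2.2 and 6.2.4:** run haematology and biochemistry at each twice-monthly visit already scheduled while albendazole continues beyond DRT+14. Word the month-6 safety panel as firm, not optional.
- **4.3.2 (items 1 and 2) and 7.6:** for any participant whose last dose falls within about four weeks of month 6, continue AE and SAE collection for a stated period after that dose, for example 28 days, with one panel after stopping.
- **Reporting:** keep six months from arm start as the common window for describing all arms, and show later events separately.

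Trigger, regimens and efficacy endpoints stay as they are.

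**Cost.** Wording in four sections, about 7 to 9 interim panels plus one after stopping for at most one participant on continuous albendazole, and at most one extra visit per affected participant. Blood volume is not an obstacle. At 2.7 + 2.7 = 5.4 mL per blood visit, 25 visits (DRT0 day 28) give 135.0 mL and 27 visits (day 56) give 145.8 mL. Adding five immunology draws of 10 mL and one post-stop panel of 5.4 mL gives 190.4 and 201.2 mL, against the 500 mL cap in 7.1.2 (pregnancy tests and screening serology not counted). The downside is slightly unequal observation time outside the common window.

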### Exploratory endpoints

1. Immunological endpoints include circulating and *in vitro* inducible cytokine levels and markers of eosinophil activation measured at baseline, during and after albendazole/ivermectin treatment and at the end of follow-up.

## Timeframe

The trial is set to start including participants as soon as ethical clearance is obtained (e.g. by October 2017), since the underlying BuDiLoLo study has already started screening subjects. The recruitment phase ends once sufficient participants (n=42) are included for the overall design of the trial. The duration of the recruitment phase thus depends partially on the screening rate in BuDiLoLo, but is anticipated not to exceed ~2 months. Arms 1 and 2 of the trial will commence as soon as recruitment is completed and randomization is performed. Arms 3 and 4 will commence in parallel thereafter. Follow-up in each study arm will last 6 months. Thus the total duration of the trial is anticipated to be ~9-10 months.

# Study population

## Context

All study participants for this treatment trial will be recruited amongst study subjects enrolled in the ongoing Burden of Disease in *Loa loa* (BuDiLoLo) study. The aims and design of this study are described the BuDiLoLo study protocol. Briefly, the primary objective of the BuDiLoLo study is to assess the burden of disease, including DALYs lost and economic impact, caused by *Loa loa* on the local population in central Gabon. The study is cross-sectional in design and based in & around the town of Fugamou in the Tsamba-Magotsi department, Ngounié province and in the neighbouring Moyen-Ogooué province, Gabon. Ngounié is considered highly endemic for *L. loa*, with an estimated prevalence of +-18% ([3](#_ENREF_3), [24](#_ENREF_24)); in contrast, Moyen-Ogooué is considered low-endemic for loiasis. 1000-2500 subjects of all ages (≥2 years) from randomly selected households in a random sample of villages will be included with the target of obtaining ≥700 *Loa*-infected individuals. Subjects will be interviewed using the WHO-validated RAPLOA questionnaire and a single blood draw will be performed for amongst others the detection/quantification of *L. loa* and *Mansonella* spp. microfilaria by thick smear microscopy, leukocyte concentration techniques and PCR.

Adult both sex subjects with *L. loa* infection levels < 50,000 mf/mL will be considered eligible for participation in the treatment study. Once sufficient participants are included for the entire study design (see below), they will be randomized to one of four study arms, which will commence semi-sequentially as described above.

## Study size

This study is a descriptive study and is not powered for statistical testing of a predefined hypothesis. As a proof of principle study, this trial aims to describe the crude effect of respective treatment regimens on the proportion of subjects achieving sustained reduction in peripheral microfilaraemia and on the kinetics of parasitaemia. For this purpose a total of 8 evaluable subjects per treatment arm is required at the end of 6-months’ follow-up. In order to allowing for up to ⅓ (33%) loss to follow-up during this period, 12 patients will be recruited into each treatment group. An additional 6 patients will be recruited for the control group for the description of the natural variability of microfilaraemia. Thus the total study size will be 42 participants: n=6 in study arm 1 and n=12 each in arms 2-4. In case of drop out of more than 33% in any study arm for evaluation of the primary endpoint, further patients will be screened and included in the respective study arm to achieve at least 8 evaluable patients in each treatment group.

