# Trial design

The overall rationale for this trial is to assess the efficacy and sustainability of available drugs in the reduction of microfilaremia in *L. loa*-infected patients in a highly endemic region of Gabon. This pilot study to be performed at the Centre de Recherches Médicales de Lambaréné (CERMEL), is designed to identify promising drug regimens for further evaluation in adequately powered comparative trials. Study outcomes will thus consist of a descriptive analysis aiming to provide the required information for the further development and evaluation of appropriate drug regimens.

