## Endpoints

### Primary endpoints

1. Primary efficacy endpoint will be the proportion of subjects with *L. loa* microfilarial levels <100 mf/mL at 6 months after the commencement of treatment
2. Co-primary efficacy endpoint will be the proportion of subjects without microscopically detectable microfilariae (assessed on three consecutive days) at any time point during follow up.

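### The protocol aims to describe sustained reduction, but no endpoint requires a low count to last, and month 6 falls at very different times after the last drug across arms

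*Protocol*

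**What the plan says.** Section 4 (Trial design) gives the rationale as to "assess the efficacy and sustainability of available drugs in the reduction of microfilaremia". Section 5.2 (Study size) names the quantity to be described as "the proportion of subjects achieving sustained reduction in peripheral microfilaraemia", together with the kinetics of parasitaemia. Section 4.2.2 adds, as secondary objectives, the duration of effect of one or two albendazole courses and of a single ivermectin dose. The word sustained is not defined anywhere in the protocol.

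The endpoints are narrower:

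- Primary (4.3.1): "microfilarial levels <100 mf/mL at 6 months after the commencement of treatment".
- Co-primary (4.3.1): no microfilariae on microscopy over three consecutive days, reached at any point in follow-up.
- Secondary efficacy (4.3.2): amicrofilaraemia at 6 months, median reduction at each month from start of treatment and at nadir, and median time to nadir.

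Follow-up runs for 6 months from the start of each arm (4.1). Arm 2 takes drug for three weeks only. The second round in arms 3 and 4 begins once 90% of arm 4 subjects still in follow-up are below 4000 mf/mL (6.1). If that has not happened by week 8, visits become less frequent and the wait goes on; no latest date is set (6.1.3, 6.1.4). After the second round, "twice monthly follow up visits will be scheduled for the remaining follow-up period until the end of follow-up at 6 months". Microfilaraemia is counted at every follow-up visit (6.2.4).

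**The concern.** A reader of sections 4 and 5.2 expects a per-subject measure of whether a low count lasts. Neither primary endpoint gives one. A subject who first falls below 100 mf/mL at month 6 is a success on the first, and a subject who clears briefly and relapses is a success on the second. The secondary endpoints are medians, a nadir and a month-6 state, all on the clock that starts with the arm.

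The month-6 value also carries different information on durability by arm. In arm 2 it is a late reading long after drug. In arms 3 and 4 it follows the last drug by an interval that is unknown in advance and could be short. The trial exists to pick regimens for larger studies. If month-6 proportions are presented as sustained reduction, part of any difference between arms may reflect time since last drug, and the report would claim more about durability than was observed.

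**Working it through.** **The plan's own figure.** Section 5.2 states that "a total of 8 evaluable subjects per treatment arm is required" and allows "up to ⅓ (33%) loss to follow-up during this period". 8 / (1 − 1/3) = 12 per treatment arm, and 3 × 12 + 6 = 42, matching "n=6 in study arm 1 and n=12 each in arms 2-4". The size reproduces, and nothing below changes it.

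**Weeks from last drug to the month-6 reading.** Take 6 months as 26 weeks and let s be the week in which the second round starts. The protocol does not give s, so it is an assumption shown as a range.

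- Arm 2: 26 − 3 = 23.
- Arm 3, two-week second course (4.1, 6.1.3): 26 − (s + 2).
- Arm 3, three-week second course (6.3.1): 26 − (s + 3).
- Arm 4, ivermectin: 26 − s.
- Arm 4, not below 4000 mf/mL: albendazole is continued and may run to the end of follow-up (6.1.4), so the interval can be 0.

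| s (week) | Arm 2 | Arm 3, 2-week | Arm 3, 3-week | Arm 4, ivermectin |
| --- | --- | --- | --- | --- |
| 4 | 23 | 20 | 19 | 22 |
| 8 | 23 | 16 | 15 | 18 |
| 12 | 23 | 12 | 11 | 14 |
| 16 | 23 | 8 | 7 | 10 |
| 20 | 23 | 4 | 3 | 6 |

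Sections 6.1.3 and 6.3.1 give different lengths for arm 3's second course and must be reconciled; the difference moves the arm 3 interval by one week.

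**Is a late start plausible?** Section 3.2.3 cites a fall to 20% of the pre-treatment level at 6 months after albendazole. At that figure, a baseline above 4000 / 0.2 = 20,000 mf/mL would still exceed 4000 mf/mL at month 6, while eligibility extends to just under 50,000. With 12 subjects in follow-up, 11 must be below 4000 (11/12 = 92%; 10/12 = 83%). If the decline is assumed log-linear, a baseline of 10,000 reaches 4000 at 26 × ln(0.4)/ln(0.2) ≈ 15 weeks, and 15,000 at 26 × ln(4/15)/ln(0.2) ≈ 21 weeks. So a late start is possible, though it depends on the baselines enrolled.

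**How far would a second albendazole course have acted?** On the same curve, the reduction is 1 − 0.2^(18/26) = 67% at 18 weeks after a course starts (s = 8) and 1 − 0.2^(10/26) = 46% at 10 weeks (s = 16). These figures are illustrative only. The protocol calls the decline gradual and does not give its shape. The cited study used 400 mg/day for 21 days, whereas this trial gives 800 mg/day. And a percentage reduction is not the <100 mf/mL endpoint.

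**Stated aim against endpoints**

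| Stated aim | Endpoint that would show it |
| --- | --- |
| Proportion with sustained reduction (5.2) | None requires more than one low time point, apart from three consecutive days at any time |
| Duration of albendazole effect (4.2.2) | Monthly medians from start of treatment; nothing from last drug |
| Duration of ivermectin effect (4.2.2) | The same; nothing from the ivermectin dose |

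**The case against.** Comparing whole regimens at a common time from their start is a coherent strategy comparison, and the second course is part of the regimen. Section 5.2 is explicit: "This study is a descriptive study and is not powered for statistical testing of a predefined hypothesis". No section ranks arms on durability. Sustained could be read loosely as still low at 6 months, since section 5.2 asks for evaluable subjects at that point. The monthly medians and time to nadir also describe the time course, and the SAP, which section 9.1 refers to, may tabulate more. An early second round shrinks the difference: at s = 4 the intervals are 20 and 22 weeks against 23.

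Much of this stands. The month-6 endpoint is legitimate, and arm 2's reading does carry durability information. What does not go away is that the stated aim and the endpoints are both fixed in the protocol and do not match. Medians across subjects do not give a proportion of subjects whose reduction lasted.

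Four stronger readings are tempting, and the protocol does not support them:

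- A reader might infer that ivermectin is flattered because it is read near its peak. Section 3.2.2 cites reductions of 70–90% lasting up to 1 year (at a different stated dose), so readings at 6 and 18 weeks would both lie within the effect.
- A reader might infer that the primary endpoint should be replaced by a sustained one. With a gradual decline, subjects may first cross 100 mf/mL close to month 6, so success could fall by an unknown amount, and requiring three late counts would put the 8 evaluable subjects at risk.
- A reader might want the arms compared at equal weeks since last drug. The shared interval can be 0, and such alignment mixes in differences in time since start.
- A reader might take it as settled that the primary endpoint is one count on one day. Section 4.3.1 names one time point and no repeat, but the SAP could set a window or a confirmatory rule.

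**Conclusion.** The point holds as a mismatch between aim and endpoints, and it should be corrected. The protocol promises sustained reduction and duration of effect, yet no efficacy endpoint requires a low count to persist or is timed from the last drug.

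Its size is the spread in time since last drug at month 6: 23 weeks in arm 2, against 16 to 4 in arm 3 (two-week course) and 18 to 6 in ivermectin recipients for starts at weeks 8 to 20, and down to 0 on continuous albendazole. The start weeks are assumptions, and an earlier start narrows the spread. How much this shifts the success proportions cannot be computed from the protocol. The finding therefore limits what may be concluded about sustainability in arms 3 and 4. It does not show that the primary endpoint is invalid or that a particular arm is favoured.

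**What to change.** 1. Keep <100 mf/mL at 6 months from commencement as the primary endpoint. In sections 4, 4.3.1 and 5.2, describe it as a whole-regimen result from start of arm, and remove the suggestion that it measures sustained reduction.
2. Add to 4.3.2 a supportive endpoint: <100 mf/mL at each of the last three scheduled twice-monthly counts, including month 6 (roughly weeks 22, 24 and 26). State the rule for missed visits and use the same denominator as the primary endpoint.
3. Beside both proportions, report the distribution of weeks from last drug to month 6 by arm, with arm 4 split into ivermectin and continuous albendazole. This is needed because the supportive endpoint does not equalise the arms: with s = 20 and a two-week course, arm 3's last dose falls at about week 22, so its three counts begin as dosing ends.
4. Limit any statement on sustainability in arms 3 and 4 to the interval actually observed.
5. Reconcile the length of arm 3's second course between 6.1.3 and 6.3.1.

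Cost: endpoint wording and a little extra analysis. Sample size and visits do not change, because the counts are already drawn. On a common denominator the supportive proportion can only equal the month-6 proportion or fall below it, by an amount that cannot be predicted from the protocol.
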